#### **TRACT infusion and related toxicities**

TRACT cellular product that has met the release criteria as specified in the IND will be infused on day +60 post kidney transplant. Release of TRACT product for clinical use will be obtained from the GMP laboratory Director and the approval for infusion will be granted by the PI based upon the Certificate of Analysis (COA) of the cellular product.

The Tregs will be infused under the supervision of the PI for the study through a large bore (≥18G) peripheral IV at a flow rate of no greater than 10cc/minute. Hemodynamic and clinical monitoring of the research subject by study personnel will be carried out with infusion documentation every 15 minutes during the infusion and for an hour following the end of the infusion.

Subjects will be monitored every 15 minutes starting with the initiation of the Treg infusion and then at 15 minute intervals. Monitoring will be carried out by the PI/Research Study Nurse for an hour after the completion of the Treg infusion. Routine monitoring will be continued during the 4 hours post infusion by the Clinical Research Unit nurse assigned to the research subject (CRU). Dose limiting toxicities will be evaluated for at least 21 days post infusion.

The patient will be under careful monitoring during and after infusion of the nTreg to monitor for any changes which may indicate hypersensitivity or other infusion related toxicities. Potential toxicities related to the Treg infusion based upon published clinical experience (40) include vomiting, hypertension, hypotension, headache, fever, sinus bradycardia and sinus tachycardia.

Monitoring will include monitoring of respiration, changes in blood pressure, angioedema, etc. The infusion will be done in the Northwestern Clinical Research Unit, which is well stocked with supportive medication such as steroids and norepinephrine, if these are required on an emergent basis. Premedication with corticosteroids (100 mg hydrocortisone), diphenhydramine and acetaminophen is routinely performed as prophylaxis for adverse infusion-related side effects.

### **2.3 Dose Rationale**

A key aspect of using Tregs for therapeutic cell transfer is achieving a marked reduction in the total pool of T cells in order to facilitate successful dynamic immune regulation by the limited number of infused Tregs. We have elected to use Alemtuzumab (Campath-1H) for robust lymphodepletion in this Phase 1 trial. The dosing strategy for Campath-1H proposed in this study is based upon our extensive single center experience in kidney/pancreas transplantation in well over 2000 patients, much of which has been published (46, 47). In addition, it draws upon the additional published experience of Campath-1H in renal transplantation (48). Importantly, a recently published randomized prospective clinical trial of Campath induction as compared to polyclonal Thymoglobulin (INTAC study, Hanaway M et al, N Engl J Med. 2011) demonstrated safety and efficacy of Campath induction in renal transplant recipients, with superior lymphodepletion using Campath as compared to Thymoglobulin. In our experience, Alemtuzumab facilitates early CNI conversion and steroid free maintenance immunosuppression with a low (< 10%) incidence of acute rejection. Dosing of tacrolimus, MMF, and Sirolimus in this study is based upon published experience with the use of these agents to achieve therapeutic effect/desired blood levels and represent standard of care approaches to maintain immunosuppression management.

The cell dosing strategy proposed for TRACT is based upon a desire to ascertain the safety of TRACT infusion using cell numbers that straddle the projected therapeutic window based upon the need for sufficient Tregs to interact with the overall conventional T cell population. As such this will provide the safety data for subsequent phase 2 trials which will examine efficacy of TRACT to provide donor specific immune regulation allowing for the safe withdrawal of drug based immunosuppression.

The cell dosing proposed in our IND is based upon our current understanding of how Tregs control immune responses – namely that the ratio of Tregs to conventional T cells is of tremendous importance. Studies have demonstrated that a high ratio of Tregs to conventional CD4+ T cells (Tconv), such as 1:1 – 1:2, is needed to prevent transplant rejection (42, 43). A high prevalence of Tregs is therefore needed to thwart rejection by establishing a dominant tolerogenic milieu through bystander suppression that is later maintained locally by infectious tolerance (44, 45). Considering the relatively small percentage of nTregs at normal steady state in peripheral blood of humans (< 5% of circulating CD4+ T cells), a change of Tconv to Treg balance is needed, and we believe best achieved through the deletion of host donor-reactive T cells using T cell depleting antibody (Alemtuzumab), followed by the infusion of an appropriate number of expanded nTregs. A review of total numbers of Tconv cells and Tregs in humans, and the efficacy of clinically available strategies for T cell depletion, is essential to the design of a rational approach to the clinical application of Tregs. As detailed by Tang et al, lymphodepletion using T cell depleting monoclonal (Alemtuzumab) or polyclonal antibodies (Thymoglobulin) can reduce the CD4+ Tconv pool by 95-99% to approximately  $4.6 \times 10^9$  cells

(52). We have designed our Phase 1 trial to provide the delivery of Tregs in numbers that would span the expected residual number of Tconv cells following lymphodepletion as described with alemtuzumab, achieving a comparably high ratio of Treg to Tconv. In our TRACT IND, we have demonstrated the ability to isolate and expand sufficient nTregs in our GMP facility from leukopheresis product to consistently achieve a desired Treg:Tconv ratio to support our TRACT clinical trial.

The starting dose we have proposed of  $0.5 \times 10^9$  cells would approximate 7 million cells/kg in a 70 kg adult recipient. This cell dose is comparable to the 20 million Treg/kg body weight cell dose used by Trzonkowska et al. in a recently reported trial of adoptively transferred Tregs to prevent remission in juvenile subjects with Type 1 diabetes (53). The Tregs used in this trial were sorted and expanded using CD3/CD28 beads in a comparable fashion to the cellular manufacturing process described in our IND. No SAEs were reported with the Treg infusions in the Trzonkowska trial. Two other published trials of adoptive therapy with Tregs can be used for further comparison. In the trial reported by Di Ianni et al (41), 4 million/kg body weight of freshly isolated Tregs were used in 5 subjects receiving an allogeneic stem cell transplant; no dose limiting toxicities related to the Treg infusion were described, despite the co-infusion of a comparable number of conventional T cells. Finally, in the trial reported by Brunstein et al (40), more than a dozen patients received selected/sorted, polyclonally expanded allogeneic Tregs at a dose of 6 million cells /kg body weight; no dose limiting toxicities were seen with these Treg infusions. The methodology used for expansion in this trial (CD3/CD28 beads, IL2, rapamycin) is very similar to that used in our manufacturing process. In summary, we believe the published clinical experience with Tregs for adoptive cell therapy support the safe use of a starting dose of  $0.5 \times 10^9$  cells using the manufacturing strategy we have proposed in our IND.

### **3 Study Objectives**

#### **3.1 Primary Objective**

Determine the safety of administering expanded Treg adoptive cell transfer (TRACT) in living donor renal transplant recipients. Additionally data will be obtained to see if TRACT leads to generation of donor specific hyporesponsiveness that may facilitate immunosuppression withdrawal and determine whether TRACT therapy leads to transplant rejection/allosensitization and/or nonspecific immunosuppression.

#### **3.2 Primary Outcome Measures**

Determine the safety profile when escalating doses of TRACT are administered to the patient population post-kidney transplant.

#### **3.3 Secondary Objectives**

The secondary objectives are to assess:

1. Incidence of adverse events developed during the duration of the study associated with renal transplantation and immunosuppression
2. Incidence, timing and severity of bacterial, viral and fungal infections
3. The absolute numbers of Treg after renal transplant in patients receiving TRACT compared to numbers of Treg prior to TRACT administration

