## 4.2 Primary Safety Endpoint

The primary safety endpoint is the evaluation of cellular related toxicities immediately and within 24 hours post-infusion of TRACT. Since TRACT is being administered to promote immunosuppression and prevent rejection, specific adverse events (subsequent rejection episodes, allosensitization, development of opportunistic infection) within 30 days of infusion will be monitored.

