## 7.6 Data Analysis

### 7.6.1 Analysis of the Primary Endpoints

Baseline descriptive statistics on all evaluable patients will be provided for demographic variables (age, sex, race/ethnicity), performance status, disease stage and status at the time of enrollment and treatment regimens previously used.

The NCI Common Terminology Criteria for Adverse Events, version 4 (CTCAE v4) will be used to evaluate toxicity. We will consider a toxicity to be an adverse event that is possibly, probably or definitely related to TRACT treatment. The maximum grade of toxicity for each category of interest will be recorded for each patient and the summary results will be tabulated by category and grade. We will describe all DLTs and other serious ( $\geq$  Grade 3) AEs on a patient-by-patient basis; descriptions will include dose level and any relevant baseline data. Data on the dose of cells they received will be tabulated.

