#### **Serious Adverse Event**

Adverse events are classified as serious or non-serious. A *serious adverse event* is any AE that is:

- fatal
- life-threatening
- requires or prolongs hospital stay
- results in persistent or significant disability or incapacity
- a congenital anomaly or birth defect
- an important medical event

Important medical events are those that may not be immediately life threatening, but are clearly of major clinical significance. They may jeopardize the subject, and may require intervention to prevent one of the other serious outcomes noted above. For example, drug overdose or abuse, a seizure that did not result in in-patient hospitalization, or intensive treatment of bronchospasm in an emergency department would typically be considered serious.

**Unrelated** ---Any reaction that is clearly due to extraneous causes AND that is likely to have been produced by the subject's clinical state or other modes of therapy administered to the subject.

**Unlikely** ---Any reaction that does not follow a reasonable temporal sequence from the study intervention (in this case TRACT infusion) OR that is likely to have been produced by the subject's clinical state or other modes of therapy administered to the subject.

**Possible** ---A reaction that follows a reasonable temporal sequence from the study intervention (in this case infusion of TRACT) OR that follows a known response pattern to the suspected drug AND that could not be reasonably explained by the known characteristics of the subject's clinical state or other modes of therapy administered to the subject.

**Probable** ---A reaction that follows a reasonable temporal sequence from the study intervention (in this case TRACT infusion) OR that follows a known response pattern to the suspected drug AND that could not be reasonably explained by the known characteristics of the subject's

clinical state or other modes of therapy administered to the subject *AND* improves with the reduction in dose or cessation of the intervention.

**Definite**---A reaction that follows a reasonable temporal sequence from the study intervention (in this case TRACT infusion and toxicities occurring during the first 24 hours post-infusion) *AND* that follows a known response pattern to the suspected therapy

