## 9.2 Recording of Adverse Events

At each contact with the subject, the investigator-sponsor and/or his designee must seek information on adverse events by specific questioning and, as appropriate, by examination. Information on all adverse events should be recorded immediately in the source document, and also in the appropriate adverse event module of the case report form (CRF). All clearly related signs, symptoms, and abnormal diagnostic procedures results should be recorded in the source document and may be grouped under one diagnosis, if appropriate (ie., cough, runny nose, sore throat, fever [all at the same time] = upper respiratory infection).

All adverse events occurring during the study period must be recorded. The clinical course of each event should be followed until resolution, stabilization, or until it has been determined that the study treatment or participation is not the cause. Serious adverse events that are still ongoing at the end of the study period must be followed up to determine the final outcome. Any serious adverse event that occurs after the study period and is considered to be possibly related to the study treatment or study participation should be recorded and reported immediately.

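### General adverse-event incidence is tied to an attributed cause, so the protocol states no all-cause, all-grade count by dose; the gap is mainly non-infectious Grade 1–2 events

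*Protocol*

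**What the plan says.** The primary outcome in Protocol section 3.2 is broad: "Determine the safety profile when escalating doses of TRACT are administered to the patient population post-kidney transplant". Section 4.2 narrows the primary safety endpoint to "evaluation of cellular related toxicities immediately and within 24 hours post-infusion of TRACT" and adds that "specific adverse events (subsequent rejection episodes, allosensitization, development of opportunistic infection) within 30 days of infusion will be monitored".

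Two secondary objectives in section 3.3 concern incidence of events. Item 1 is "Incidence of adverse events developed during the duration of the study associated with renal transplantation and immunosuppression". Item 2 is "Incidence, timing and severity of bacterial, viral and fungal infections", with no condition on cause.

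Section 7.6.1 defines what enters the toxicity table: "We will consider a toxicity to be an adverse event that is possibly, probably or definitely related to TRACT treatment". The worst grade per patient is then tabulated by category and grade. Dose level is not named as part of that layout, although the doses received are to be tabulated. A separate sentence promises a per-patient description, with dose level, of all DLTs and other events of Grade 3 or higher. That sentence states no relatedness limit.

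The causality classes are in section 9.1, under the serious adverse event definition. Their reference treatment is TRACT. The class for unlikely relation, for example, opens with "Any reaction that does not follow a reasonable temporal sequence from the study intervention (in this case TRACT infusion"). Other causes appear only as one pooled alternative: the patient's clinical condition or any other therapy. Section 9.2 then requires that "All adverse events occurring during the study period must be recorded".

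**The concern.** The trial exists to establish the safety of TRACT, yet its only objective on general adverse-event incidence is worded around the transplant and its drugs. The only summary table is worded around TRACT. Both numerators depend on a judgement of cause, made without masking and without a control arm.

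That judgement is hard here. TRACT is given to patients who have had alemtuzumab and are taking sirolimus and mycophenolate, and section 3.1 itself asks whether TRACT causes nonspecific immunosuppression. A harm of that kind would resemble the effects of the background drugs. The measure that does not depend on attribution is the count of all events by dose tier, and the stated plan does not ask for it. A dose pattern in low-grade events could then go unseen in the stated outputs, even though the events are on the case report form.

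**Working it through.** No figure in the protocol is in dispute, so the check compares texts. The only arithmetic on the design is 4 tiers × 3 patients = 12, which matches the stated enrolment.

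**Step 1: can item 1 be counted from what is recorded?** Item 1 needs a flag for events due to the transplant or to immunosuppression. The section 9.1 classes (unrelated, unlikely, possible, probable, definite) all grade relation to TRACT. An event classed unrelated or unlikely may be due to background drugs, the transplant, renal disease or an intercurrent illness, and the class does not say which. Section 7.4 requires a judgement about transplant and concomitant drugs, but only for candidate DLTs.

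**Step 2: what does the toxicity table leave out?** It needs a class of possible or higher. As most naturally read, possible and probable both require that the patient's condition or other therapy offers no reasonable explanation. The grammar also allows a looser reading in which a plausible time sequence is enough for possible. The same event could then also meet the definition of unlikely, so the class is left to discretion. Definite carries no such exclusion, but it refers to the first 24 hours, so acute infusion reactions can enter the table. The filter bites on later events.

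Section 2.1 shows how readily another explanation is found. Diarrhea is listed for mycophenolate, alemtuzumab and sirolimus; rash is listed for alemtuzumab and sirolimus. Of the seven potential Treg infusion toxicities named in section 2.2 (vomiting, hypertension, hypotension, headache, fever, sinus bradycardia, sinus tachycardia), two (hypertension and fever) are also listed by name for sirolimus, which patients are taking at day 60.

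**Step 3: which events are captured, and on what condition?**

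| Event | Where captured | Attribution limit stated? | Dose level named? |
|---|---|---|---|
| Infections, any grade | 3.3 item 2; 7.1; 7.2 | No | No |
| Rejection, allosensitization, opportunistic infection to day 30 | 4.1; 4.2 | No | Through escalation |
| Serious events to day 30 | 4.1, escalation condition | No | Through escalation |
| Patient and graft survival | 7.1 | No | No |
| Laboratory anomalies | 7.1, as an assessment only | No | No |
| Grade 3 or higher | 7.6.1, per-patient description | No | Yes |
| Grade 1–2 non-infectious, judged at least possibly TRACT-related | 7.6.1 table | Yes | No |
| Grade 1–2 non-infectious, put down to transplant or its drugs | 3.3 item 1 | Yes, by an unrecorded category | No |
| Grade 1–2 non-infectious, put down to neither | No stated summary | – | – |

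The last three rows are the gap. Section 7.6.1 also treats serious as Grade 3 or higher, whereas section 9.1 defines it by outcome. A non-infectious Grade 2 event that led to hospital admission and was judged unrelated to TRACT would be neither tabulated nor described under 7.6.1.

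**Step 4: how much can an all-cause table by tier show?** With 0 events in n patients, the one-sided 95% upper bound is 1 − 0.05^(1/n). For one tier, n = 3: 1 − 0.05^(1/3) = 0.63. For all tiers, n = 12: 1 − 0.05^(1/12) = 0.22. The table would be descriptive; it removes the attribution filter but cannot establish a dose trend.

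**The case against.** The strongest case against is that the harms that matter most are already counted without attribution. Infections are covered by item 2 of section 3.3, so an infection blamed on immunosuppression is not lost. Grade 3 or higher events come with dose level in section 7.6.1, and with 3 patients per tier all-cause counts at that grade follow directly. Thirty-day rejection, allosensitization and opportunistic infection, the 30-day serious-event condition in section 4.1, and patient and graft survival state no attribution. All of this stands and narrows the point.

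Second, the classes for unrelated and unlikely point to other therapy and clinical condition, which in these patients largely means the transplant and its drugs. That is a usable proxy, but it pools causes and is not the category that item 1 names.

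Third, all events are recorded, and a list of tables commonly belongs in a statistical analysis plan, which is not at hand. The absence of a table alone would therefore be no finding. What remains is that the protocol itself fixes the wording of item 1 and the definition of toxicity, and a plan that follows them inherits both filters.

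A reader might also infer that item 1 and the toxicity table divide the same events between them. Nothing in the text makes them mutually exclusive.

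**Conclusion.** The point holds in a limited form. The protocol ties general adverse-event incidence to an attributed cause that its own scale does not record as a category. Its one summary table is restricted to events attributed to TRACT, with dose level not named. The stated plan therefore provides no all-cause, all-grade incidence by dose, and what is missing is mainly non-infectious Grade 1–2 events.

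Three stronger readings are tempting and not supported. Item 1 is not the only incidence objective, because item 2 covers infections. It is not true that no all-cause information by dose is available, because Grade 3 or higher events are described with dose level. The safety answer as a whole does not rest on open-label attribution; that applies to the toxicity table, item 1 and the DLT definition.

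The conclusion assumes that the Grade 3 or higher sentence in section 7.6.1 is not subject to the relatedness limit just before it, and that possible and probable are read as requiring that other therapy does not reasonably explain the event. No sample size, error rate, escalation rule or data collection is affected. This is a worthwhile, inexpensive improvement, not a flaw that undermines the trial.

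**What to change.** Reword item 1 of section 3.3 to: *Incidence of all adverse events, irrespective of attributed cause, by dose tier and by period (before and after TRACT infusion).*

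In section 7.6.1, show this table beside the TRACT-related toxicity table, covering all grades, with relatedness to TRACT as a breakdown. State the length of each period, since the two differ and the earlier one contains the surgery; the comparison between them is descriptive.

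The cost is one sentence in section 3.3 and one more table. Section 9.2 already requires every event to be recorded, so no new data are needed. The drawback is a longer table that includes expected transplant events.

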## 4 Study Design

[figure not shown]

#### 4.1 General Design

This is an open label, single-center phase I study of TRACT in living donor renal transplant recipients. This safety portion of this study will continue for six months but the patients will be followed for up to 60 weeks. Participants will receive “standard of care” immune suppression, living donor kidney transplantation and TRACT. Prior to the kidney transplant, blood will be collected for immunophenotypic analysis of circulating leukocytes by flow cytometry, as well as functional immune assays. **Dose escalation of nTregs will be based upon the absence of infusion related side effects and specific adverse events (subsequent rejection episodes, allosensitization, development of opportunistic infection) within 30 days of infusion.**

Patients will undergo living donor kidney transplantation using immunosuppression based upon the standard of care regimen using alemtuzumab and the avoidance of oral corticosteroids (46, 47). This immunosuppressive regimen has been used for more than a decade at Northwestern in more than 2000 kidney transplant recipients. All patients will receive two doses of alemtuzumab (Campath-1H, 30mg); one at the time of renal transplant, and one on post-operative day two to achieve peripheral T-cell depletion. Intravenous glucocorticoids will be administered prior to Campath administration to limit cytokine release syndrome in association with this monoclonal antibody, and continued for the first two days post-transplant. Thereafter, steroids will not be used for immunosuppression. All transplant recipients will be started on oral immunosuppressive therapy with MPA and tacrolimus prior to transplant. After 30 days, patients will be converted to the combination of Sirolimus and MPA, as the inhibition of IL2 production by CNIs would impair the survival of infused expanded Tregs.

An important consideration when using lymphocyte depleting induction agents such as alemtuzumab are the pharmacokinetics of the infused antibody. Premature introduction of Tregs in a recipient with circulating levels of alemtuzumab in a therapeutic range will lead to the unfortunate destruction of the infused cells. Published data on the half-life of alemtuzumab in patients without the cellular burden of hematologic malignancies is available from studies of Campath 1H in rheumatoid arthritis (49). Half-life of Campath in subjects receiving total treatment courses of 100mg to 400mg of Campath ranged from 5 to 9 days. Therefore, the infusion of TRACT in this study will be delayed until 60 days post kidney transplant to avoid Campath-related destruction of the infused cells.

TRACT infusion will be administered 60 days after kidney transplantation. Peripheral blood samples for immune monitoring studies (flow cytometry and immune function evaluation and urine samples for biomarker assessment will be collected pre-transplant and at 1, 3, 6, 9, and 12 months post-transplant as detailed below. Kidney biopsies will be obtained in accordance with standard of care clinical practice at 3 and 12 months post-transplant.

